## Methods/Design

### Study population

Twenty primary schools within a 50 km radius of Melbourne will be involved in Transform-Us!. All year 3 children in the intervention schools will receive the program and all year 3 children in all schools will be invited to participate in the evaluation of the intervention with the aim to recruit 600 students. Due to significant increases in sedentary behaviors and declines in physical activity among children in primary school, 8-9 year olds were considered a key target population. In addition, for practical purposes a three-year study implemented in year 3 would ensure children remained at primary school throughout the entire study ensuring ease of follow-up.

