### Measurement protocol

Assessments will be conducted at baseline (Feb-May 2010), mid-intervention (Nov-Dec 2010), post-intervention (Nov-Dec 2011), and 12-months follow-up (Nov-Dec 2012). To minimize participant burden, blood pressure assessments will be taken at baseline, post-intervention and 12-months follow-up only, and blood samples will be taken at baseline and post-intervention only. All of the children's measurements (except the blood samples) will be conducted at school by trained research staff using regularly calibrated equipment. Children will complete the survey in small groups with trained research staff. The blood sample will be undertaken at a commercial pathology laboratory by a trained phlebotomist and the parent survey will be sent home to parents to complete.

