### Data analysis

All statistical analyses will be performed using Stata 9.1 for Windows (StataCorp LP) and will adjust for clustering by observations by school (the unit of randomization). All analyses will be conducted using the intention to treat principle. Generalized Estimating Equations (GEE) [84] will be used to fit regression models to describe the effects of the intervention on key outcome variables among children. Separate models will be fitted to determine differences in key outcome variables in the intervention and control groups.

Separate models will be evaluated for each assessment point (mid-intervention; post-intervention; 12 months follow-up), adjusting for baseline levels of the outcome, and, where appropriate, baseline levels of the mediating variables. PA-I and SB-I intervention conditions will be the predictors of primary interest (entered in the form of two indicator variables and their interaction term). Analyses will be performed excluding and including children who were recruited to the study after baseline. For physical activity outcomes, we will compare the PA-I and SB+PA-I versus the SB-I and C groups. For sedentary behavior outcomes, we will compare SB-I and SB+PA-I versus the PA-I and C groups. For health outcomes, we will compare C versus the other three groups and the SB+PA-I versus the single intervention groups. All models will be adjusted for measured confounders. As it has been argued that adjustment for multiple comparisons should not be used when assessing evidence about specific hypotheses no adjustment for multiple comparisons will be performed [85]. To evaluate the magnitude and direction of the intervention effects mediated by intrapersonal, interpersonal and environmental processes, the product-of-coefficient method will be used [86]. A first set of GEE regression models will assess the impact of the intervention condition (regression coefficient α) on the residualized change score of the hypothesized mediators (Table 1), after controlling for significant covariates. A second set of GEE regression models will estimate the independent effects of the intervention condition and residualized changes in the mediators (regression coefficient β) on changes in the outcome variables. The significance of the product of the regression coefficients α and β (representing the mediated effect of the intervention) will be tested using bias-corrected bootstrap methods as outlined by Pituch and colleagues [87].

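### Intention to treat is claimed, but the separate baseline-adjusted model at each visit leaves out children without a valid outcome there and does not use their mid-intervention value

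*Protocol article*

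**What the plan says.** The Data analysis section states the principle: "All analyses will be conducted using the intention to treat principle". It then names the method, "Generalized Estimating Equations (GEE) [84] will be used to fit regression models to describe the effects of the intervention on key outcome variables among children", with adjustment for clustering by school, and sets its structure: "Separate models will be evaluated for each assessment point (mid-intervention; post-intervention; 12 months follow-up), adjusting for baseline levels of the outcome". So there are three models for each outcome, each conditioning on the baseline value. On changes in the cohort the section adds only this: "Analyses will be performed excluding and including children who were recruited to the study after baseline".

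Three other places bear on who has an outcome at each visit.

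- Measurement protocol gives four assessments (baseline, mid-intervention, post-intervention, 12-month follow-up) and says "All of the children's measurements (except the blood samples) will be conducted at school by trained research staff using regularly calibrated equipment". The exceptions are blood sampling at a laboratory and the proxy report, since "the parent survey will be sent home to parents to complete".
- Under the activPAL heading, a device record counts only with four valid days, one of them at a weekend. This rule applies to both devices.
- Study population gives a reason for choosing year 3: it "would ensure children remained at primary school throughout the entire study ensuring ease of follow-up". Sample size calculations assumes 91% retention.

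The primary aim names post-intervention and 12-month follow-up as the time points of interest. Teacher training says the tapered third year is meant to allow maintenance to be examined.

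**The concern.** A model fitted visit by visit, with baseline as the only earlier value of the outcome, uses only the children observed at that visit. A child measured at baseline and mid-intervention, and then absent, moved or without enough wear, is outside both models that answer the primary aim. The best available predictor of the missing value, the same outcome at mid-intervention, is in hand but has no role there. That is an available-case analysis carrying an intention-to-treat label.

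Two things are at stake.

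- **Bias.** Ordinary GEE on available cases needs loss to be unrelated to the outcome given arm, baseline and the adjusted confounders. If children who were less active at mid-intervention are lost more often in one arm than in another, that condition fails. The value that would repair it is left out.
- **Comparability between visits.** Three models on three possibly different sets of children mix true maintenance with change in composition. The post-intervention to 12-month comparison is the one the tapered year was built for.

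**Working it through.** **1. The plan's own figures, and whether loss threatens power.** Inputs from Sample size calculations: standardized difference 0.32, two-sided 0.05, power 0.8, retention 91%, ICC 0.018, 20 schools, 30 per school.

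- Per group: 2 × (1.960 + 0.842)² / 0.32² = 153.3, so 154 per group and 308 in total.
- Retention: 308 / 0.91 = 338.5, or 16.9 per school, rounded to 17 × 20 = 340. This matches.
- Clustering: 1 + (30 − 1) × 0.018 = 1.522; 338.5 × 1.522 = 515, or 25.8 per school, rounded to 26 × 20 = 520. This matches.
- After 9% loss from 600: 546 analysed, 27.3 per school, design effect 1 + 26.3 × 0.018 = 1.473, effective n = 371. Power is 0.87 by the normal approximation, or 0.83 with t on 18 df.

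Power at the planned loss is adequate, so the question is bias and the label.

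**2. Which children enter which model, as written.**

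| Valid outcome at | Mid model | Post model | 12-month model |
|---|---|---|---|
| Baseline, mid, post, 12 months | yes | yes | yes |
| Baseline, mid, post | yes | yes | no |
| Baseline, mid | yes | no | no |

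Nothing stated in the section carries information from the mid column into the other two.

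**3. Size of the bias (simulation; the inputs are assumptions except 0.32 and 9%).** Baseline, mid and post values have SD 1 and pairwise correlation 0.6. Treated children gain 0.32 at mid and post. Every child has a mid value. Loss after mid follows logit P(loss) = c − s × mid value, with s = 0.5 or 1.0 per SD. The available-case estimate is the arm coefficient from regressing post on arm and baseline among children observed. The comparison first fills in missing post values by regression within arm on baseline and mid.

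| Loss mechanism | 9% loss, s = 0.5 / 1.0 | 20% loss, s = 0.5 / 1.0 |
|---|---|---|
| Treated only, equal total loss by arm | 0.33 / 0.34 | 0.34 / 0.36 |
| Same in both arms, equal total loss | 0.32 / 0.32 | 0.32 / 0.32 |
| Same slope and same intercept in both arms | 0.31 to 0.32 | 0.31 to 0.32 |
| Any of these, mid value used | 0.32 | 0.32 |

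Under the treated-only mechanism the excess is about 0.01 to 0.02 SD at 9% and 0.02 to 0.04 SD at 20%. On the protocol's SD of 18 min/day for physical activity this is 0.01 × 18 = 0.2 to 0.02 × 18 = 0.4 min/day, and 0.4 to 0.7 min/day. When loss depends on activity alike in both arms, the shift among those retained nearly cancels.

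**4. Precision.** Let d be the share missing at post, q the share of those with a mid value, and r the mid/post correlation given baseline. Relative to one child's variance per unit of sample:

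- available cases: 1 / (1 − d)
- using mid: (1 − r²) / (1 − d) + r² / (1 − d + qd)

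At d = 0.09, r = 0.7, q = 1: 1.099 against 0.51 × 1.099 + 0.49 = 1.050, a gain of 4.6%. At r = 0.3, q = 0.5 the gain is 0.4%. At d = 0.20 the range over the same inputs is 1.0% to 10.9%.

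**The case against.** The best case for the plan is that a baseline-adjusted model at each visit is a standard trial analysis. The article names no complete-case rule, and separate models can be fitted after multiple imputation. Missing-data handling is commonly left to an analysis plan, which is not shown here, so silence on imputation is not a fault. Nothing in the section moves children between arms or removes them for poor adherence. Loss is allowed for in the sample size, and the upward bias appears only under an arm-specific mechanism for which the protocol gives no evidence.

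Most of that stands and limits the point. What remains is that the article does more than stay silent: it fixes a structure that conditions each visit on baseline alone, although the same outcome is measured repeatedly. The planned analyses with and without late recruits address children who join, not those who are lost.

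Some stronger readings are tempting, and the text does not support them.

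- A reader might infer that children are measured only at school, so that anyone who changes school is lost. Blood is taken at a laboratory, devices are worn through waking hours, and the parent survey goes home. The text says where measurements are done, not what happens to leavers.
- A reader might infer that mid-intervention data are thrown away. They are the outcome of their own model.
- A reader might take the Study population remark as a claim that no child changes school. It gives staying in primary school as a reason for choosing year 3.
- A reader might take the simulation as proof that the fix removes bias. Loss there depends only on a value the fix observes, so recovery of 0.32 is built in.

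**Conclusion.** The point holds in a limited form. As written, the post-intervention and 12-month estimates rest on children with a valid outcome at that visit, and earlier follow-up values of the same outcome do not inform them. The intention-to-treat label therefore claims more than the stated models deliver. The comparison between visits may also rest on different children.

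The likely size is modest: about 0.01 to 0.02 SD on 0.32 at the planned 9% loss, and 0.02 to 0.04 SD at 20%, a rate the protocol does not give. Both depend on loss being linked to mid-intervention activity differently by arm, on a correlation of 0.6 between visits and on every lost child having a mid-intervention value. With the same dependence in both arms the bias is close to zero, or slightly conservative if total loss then differs by arm. It would be wrong to conclude that the trial is underpowered or that its result would be materially distorted at the planned retention. The change is worth making because it needs no new data and rests on a weaker assumption about loss.

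**What to change.** In Data analysis, replace the separate visit models with one model for the mid-, post- and 12-month outcomes. Include the two intervention indicators and their interaction, each by visit, with adjustment for baseline and child nested in school, fitted by likelihood to all available visits. Alternatively, keep GEE and run it after multiple imputation by arm, with the mid-intervention value and school in the imputation model. Read the post-intervention and 12-month contrasts from that analysis, and analyse each child in the arm of the school of first enrolment.

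The cost is analysis wording and modest extra programming. The downside is a slightly more complex model that still assumes data are missing at random, which is weaker than the assumption now implied but cannot be verified. No change to where or how children are measured is needed.

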### Randomization

A listing of Melbourne suburban primary schools (n = 367), their enrolment number and associated suburb socioeconomic index for areas (SEIFA) score (suburb disadvantage score) will be obtained. Schools with an enrolment of over 300 students will be grouped in quintiles of SEIFA score and schools from the first, third and fifth quintiles will be selected to represent low, mid and high SEIFA strata respectively. Schools in each stratum will be randomly ordered with probabilistic weighting according to enrolment number, and will be approached consecutively and offered participation. Schools will then be randomly allocated to either SB-I, PA-I, SB+PA-I or current practice control (C).

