##### Confounders

###### Sociodemographic characteristics

Child's age and sex, family structure (e.g., siblings, number people living in household), parents' age, sex, marital status, education attainment, postcode, and country of birth will be collected in the parent survey. Children will report the number of working cars their family has, the number of holidays they went on in the last year and if they have their own bedroom to assess sociodemographic position [79].

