###### Stage of pubertal maturation

Since all children will be aged 8-9 years old at baseline, it is expected that they will all be pre-pubertal and thus the assessment of pubertal status is not considered necessary. However, to account for any potential growth (maturity) effects, growth rates (change in height) will be assessed from the height measurements taken at each assessment time point.

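### Adjusting every model for measured confounders brings change in height, which is measured after randomisation, into models declared intention to treat

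*Protocol article*

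**What the plan says.** The Data analysis section declares intention to treat for all analyses. It fits GEE models clustered by school, separately at each follow-up wave, with two intervention indicators and their interaction, and adjusts for the baseline value of the outcome. It then adds, without a list or a restriction on timing, that "All models will be adjusted for measured confounders".

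The set meant by that sentence is described once, under the heading Confounders. It has four parts: sociodemographic characteristics, general health and family history, nutritional intake, and stage of pubertal maturation. Under the last, puberty itself is not assessed. The protocol gives height growth as the substitute, and its purpose: "to account for any potential growth (maturity) effects, growth rates (change in height) will be assessed from the height measurements taken at each assessment time". Postcode appears among the sociodemographic items: "parents' age, sex, marital status, education attainment, postcode, and country of birth will be collected in the parent survey". How it would be coded is not stated.

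SEIFA is not among the listed confounders. It appears in the Randomization section, where "schools from the first, third and fifth quintiles will be selected to represent low, mid and high SEIFA strata respectively". Schools are then allocated at random to the four arms, and the section does not say whether this is done within stratum.

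**The concern.** A confounder list in a randomised trial should hold only variables fixed before the intervention can act. Change in height is not one of them. The same paragraph specifies baseline values for the outcome and for the mediators, but sets no such limit on the confounders, so following the text puts a post-baseline variable into each effect model.

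What is at stake is the meaning of the coefficient. If the intervention affects growth at all, the adjusted coefficient omits whatever part of the effect runs through growth. It can also pick up causes shared by growth and the outcome. BMI is the sharpest case, because height is in its denominator and the economic evaluation converts BMI change into cost per BMI unit and cost per DALY.

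Postcode is a side issue under the same sentence. Treatment is constant within a school, so a categorical covariate that nearly follows the school boundaries competes with the treatment terms.

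**Working it through.** **Timing.** Under Measurement protocol, height is available at baseline (February to May 2010) and at three later waves (November to December of 2010, 2011 and 2012). The Study Protocol Overview starts the intervention at the end of Term 2, 2010. The earliest change in height is therefore known only at the mid-intervention wave.

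**Direct bias from adjusting for growth.** Let g be the intervention's effect on height growth (cm) and s the slope of the outcome on growth (units per cm). The adjusted coefficient differs from the total effect by -(g x s). The document gives neither value, so both are assumed:

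| g (cm) | s = 0.05 BMI units/cm | s = 0.1 BMI units/cm |
|---|---|---|
| 0 | 0 | 0 |
| 0.1 | -0.005 | -0.010 |
| 0.3 | -0.015 | -0.030 |

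I do not express this as a share of the planned BMI effect. The BMI figures under Sample size calculations (1.9 with SD 0.25) give 1.9/0.25 = 7.6, not the stated standardised difference of 0.32, so they are no usable yardstick.

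**Postcode as categories.** Inputs from the protocol: 20 schools, 30 children per school, ICC 0.018, 2 x 2 factorial. Assumed: five schools per arm, one home postcode per school, a share of children living in a neighbouring school's postcode, and postcode entered as dummy variables. The quantity is the generalised-least-squares variance of the PA main effect (PA coefficient plus half the interaction) with the dummies, divided by the variance without them. The figure shown is the median over 100 random allocations.

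| Share living in a neighbouring postcode | Variance ratio |
|---|---|
| 0% | effect not estimable |
| 10% | 4.3 |
| 25% | 2.2 |
| 50% | 1.4 |

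**SEIFA.** Assume strata of 7, 7 and 6 schools and simple allocation to four arms of five. In 100,000 simulated allocations, about 71% leave at least one arm without any school from some stratum, and about a quarter give some arm four or more schools from one stratum. These figures describe chance imbalance, not bias.

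**Degrees of freedom.** An intercept, two indicators and their interaction leave 20 - 4 = 16 at school level. Two stratum terms leave 14.

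**The case against.** The best defence is that growth is a sensible prognostic variable in children of this age. Nothing in the protocol suggests that standing lessons or playground equipment change how fast a child grows. If they do not, the direct bias is zero, and adjusting for growth merely removes noise. This stands as an argument about size, above all for the accelerometer outcomes. It does not justify fixing in advance a rule whose validity depends on that assumption, when baseline covariates need no such assumption.

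A closed covariate list might also sit in an analysis plan that is not shown. That is possible, but such a list would have to depart from the published sentence to avoid the problem.

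Several stronger readings are tempting, and the document does not support them:

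- **Postcode absorbs the treatment effect.** This follows only if postcode is entered as categories. It is listed among the parents' items, its coding is not given, and it may be collected to derive an area index, which would do no such harm.
- **Leaving SEIFA out biases the result.** It does not bias a randomised comparison. It costs precision or leaves chance imbalance unadjusted. Nor does the protocol say that allocation ignored the strata; it is silent.
- **Diet lies on the causal path.** This would matter only for follow-up values, and the wave to be used is not stated.
- **Parent-survey covariates lose children and power.** Handling of missing covariates is not stated. With an assumed 15% non-response, 600 x 0.91 = 546 becomes 464, and power for 0.32 at ICC 0.018 falls from 0.87 to 0.83 (normal approximation), still above the planned 0.8.

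**Conclusion.** The point holds in a limited form. Taken together, the blanket adjustment rule and the confounder list put a post-randomisation variable into models described as intention to treat. That is in the text and does not depend on anything left unsaid. The consequence is that the coefficients are not guaranteed to estimate the intended effect, most clearly for BMI and the cost-effectiveness ratios built on it.

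The size is probably small: the tabulated range rests wholly on assumed growth effects and slopes. It covers only the direct term. Any contribution from shared causes of growth and the outcome cannot be computed from the document. The postcode and SEIFA remarks are advice on how to write the covariate list, conditional on coding and allocation details that the protocol does not give. They are not evidence of bias.

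**What to change.** Replace the blanket sentence with a closed list of baseline covariates for all intervention-effect models: baseline outcome, baseline age, sex, and the other baseline sociodemographic items the investigators want. State that change in height and any diet measure taken at follow-up are excluded from these models. Growth may be used in one sensitivity analysis of BMI, labelled as such.

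Do not enter postcode as a categorical factor. Use the SEIFA stratum, already known for every school, and describe it as a precision and chance-imbalance term. State whether schools were allocated within stratum.

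The cost is a change of wording, with no new data. The one statistical price is two school-level degrees of freedom for the stratum.

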### Sample size calculations

It is expected that the intervention effects on behavioral and biological primary outcomes will be moderate in size (standardized difference ~ 0.32, equivalent to a mean change in objectively-measured PA of 8 minutes per day [SD = 18 min] and a change in body mass index (BMI) units (age-sex difference from population norm data) of 1.9 kg/m^2 ^[SD = 0.25]) [25,46]. Without accounting for school cluster effects, the number of participants needed to detect a standardized difference of 0.32 with 0.8 power for sedentary behavior (SB-I) and physical activity (PA-I) alone and in combination (SB+PA-I), using a significance level of 0.05 with a two-tailed test, assuming a retention rate of 91% (based on the team's previous experience) and 20 participating schools, would be 340 in total (17 per school). With a previously observed school clustering effect of 0.018 (intra-class correlations [ICCs] for sedentary behavior, physical activity and BMI outcomes estimated using data from a previous intervention study)[44], the minimal total number of participants needed is 520, i.e., 26 per school. Hence, we will conservatively recruit 30 participants per school, giving a total sample size of 600 participants.

Moderate mediated effects of the intervention on the behavioral outcomes are expected (here a moderate mediated effect size is defined as standardized regression coefficients α and β of ~ 0.39)[47]. According to a 2007 simulation study by Fritz and MacKinnon [48], to detect a moderate mediated effect size with 0.8 power, using a significance level of 0.05 with a two-tailed test and bias-corrected bootstrap methods, ~ 61 independent observations are needed. If we assume a 9% rate of loss to follow-up, an average school cluster effect of 0.03 for the mediators (ICCs estimated using data from a previous intervention study)[44] and an average of 30 observations per school (see above), the sample size needed to detect a moderate mediated effect size would be 100 (20 per school). Hence, the sample size needed to detect moderate intervention effect sizes with 0.8 power for the primary outcomes (n = 600) will also be sufficient to detect a moderate-sized effect with 0.8 power for the mediating variables.

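### The mediation models use a different covariate rule from the effect models and do not state adjustment for the baseline outcome, so on a literal reading the mediator-to-outcome path can be materially biased

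*Protocol article*

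**What the plan says.** All the relevant text is in the Data analysis section of the protocol article.

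- **Effect models.** They are fitted separately at each assessment point, "adjusting for baseline levels of the outcome, and, where appropriate, baseline levels of the mediating variables".
- **Covariates, general rule.** "All models will be adjusted for measured confounders".
- **Mediation, method.** For mediated effects "the product-of-coefficient method will be used".
- **Mediation, α models.** These assess the impact of condition "on the residualized change score of the hypothesized mediators (Table 1), after controlling for significant covariates".
- **Mediation, β models.** These estimate the independent effects of condition and of "residualized changes in the mediators (regression coefficient β) on changes in the outcome variables".

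The β sentence names neither the baseline outcome nor a covariate set. It does not say whether the outcome change is raw or residualized. The section does not say whether the earlier baseline and confounder rules carry over to the mediation models.

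**The concern.** Two things do not fit together.

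First, adjustment for all measured confounders and control for significant covariates cannot both govern the α models. The first is one fixed set. The second is chosen by p-value and can differ from mediator to mediator.

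Second, the β sentence calls the mediator changes residualized but the outcome changes simply changes, which reads naturally as raw change. A raw change is related to its own baseline through regression to the mean. Condition is randomized but the mediator is not. If baseline behavior also predicts how a mediator such as enjoyment, self-efficacy or parental rules changes, leaving the baseline outcome out confounds β.

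At stake is the secondary aim of identifying what mediates the intervention. Two analysts following this text could report materially different mediated effects from the same data.

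**Working it through.** The protocol gives no figure for this point, so there is none to reproduce. The check compares the specifications, derives the bias, and sizes it by simulation.

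**1. Specifications side by side**

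| | Effect model | α model | β model |
|---|---|---|---|
| Response | Outcome at each assessment | Residualized mediator change | Outcome change, type not stated |
| Baseline outcome | Yes | Not named | Not named |
| Covariates | Measured confounders | Significant covariates | Not named; general rule may apply |

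**2. Inputs**

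- From Sample size calculations: "a moderate mediated effect size is defined as standardized regression coefficients α and β of ~ 0.39"; a total effect of "standardized difference ~ 0.32"; and "we will conservatively recruit 30 participants per school, giving a total sample size of 600 participants", in 20 schools.
- Set to match: a direct effect of 0.16, so the total is 0.16 + 0.39 × 0.39 = 0.312.
- Assumed, not in the documents: outcome stability given baseline, r = 0.3, 0.5 or 0.7; correlation of baseline outcome and baseline mediator, ρ = 0.3; effect of baseline outcome on the later mediator given the baseline mediator, λ from −0.2 to 0.3.
- Simplification: condition is one two-group contrast, not the two indicators and their interaction.

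**3. Bias of β with raw change and no baseline term**

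Write follow-up outcome = r × baseline outcome + β × mediator + direct effect × condition + error. Subtracting the baseline leaves (r − 1) × baseline outcome in the change. If that term is left out, with standardized baselines,

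bias in β = (r − 1) × λ × (1 − ρ²) / V,

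where V is the variance of the residualized mediator within condition. The bias is zero when λ = 0.

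**4. Estimated β, true value 0.39 (1,000,000 simulated children per setting)**

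| λ | Raw change, r = 0.3 | r = 0.5 | r = 0.7 | Residualized change | Baseline outcome and mediator included |
|---|---|---|---|---|---|
| −0.2 | 0.58 | 0.52 | 0.47 | 0.38 | 0.39 |
| 0 | 0.39 | 0.39 | 0.39 | 0.39 | 0.39 |
| 0.1 | 0.29 | 0.32 | 0.35 | 0.38 | 0.39 |
| 0.2 | 0.20 | 0.26 | 0.31 | 0.35 | 0.39 |
| 0.3 | 0.12 | 0.20 | 0.28 | 0.32 | 0.39 |

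At r = 0.5 the raw-change errors are −18%, −34% and −48% for λ = 0.1, 0.2 and 0.3, and +34% for λ = −0.2. The whole grid runs from −68% to +48%. Adding the baseline outcome alone to the raw-change model gives 0.36 to 0.41.

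**5. Formula against simulation**

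At r = 0.5 and λ = 0.2 the simulated error is 0.39 − 0.256 = 0.134 = 0.5 × 0.2 × 0.91 / V, so V = 0.679. Removing λ² × 0.91 = 0.036 leaves 0.643. At λ = 0.3, V is then 0.643 + 0.082 = 0.725 and the predicted β is 0.39 − 0.5 × 0.3 × 0.91 / 0.725 = 0.202, against 0.201 simulated. At r = 0.3 and λ = −0.2 the prediction is 0.39 + 0.7 × 0.2 × 0.91 / 0.679 = 0.578, against 0.579.

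**6. Effect on α, the product and the total**

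- α is 0.387 to 0.391 in every setting, so it is not affected.
- The true product is 0.39 × 0.39 = 0.152. At r = 0.5 it becomes 0.39 × 0.256 = 0.100 for λ = 0.2 and 0.39 × 0.523 = 0.204 for λ = −0.2. If α is zero, the product is zero whatever β is.
- In 2,000 simulated trials of 600 children without clustering (r = 0.5), direct plus mediated effect from the raw-change models differed from the baseline-adjusted main effect by −0.001 on average, with SD 0.029 to 0.036. The SD of the main effect itself was about 0.07.

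**7. Test of β when the mediator has no effect**

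In a separate simulation (20 schools of 27 children, ICC 0.018, r = 0.3 to 0.7), the raw-change test of β rejected in 19–23% of trials when baseline behavior predicted mediator change with slope 0.1, and in 57–68% at slope 0.2. With the baseline outcome included it rejected in about 5%. This is the test of β, not the bootstrap test of the product that the protocol plans.

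**The case against.** The strongest reply is that baseline adjustment is stated earlier in the same section. The clause on baseline mediators makes most sense if it is meant to reach the mediation models. If it does, raw change and follow-up value give identical coefficients and the bias disappears. The plain word for change may also be shorthand for residualized change, where attenuation is at most 18% in the grid. The p-value rule is attached only to the α models, where randomization limits confounding, and no size has been worked out for it. The dependence that drives the bias is assumed and could be zero. A condensed article may also leave the exact mediation covariates to an analysis plan.

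Much of this stands: the β specification is ambiguous, not a proven omission. But the earlier sentence describes models whose main predictors are the intervention indicators, and it brings in baseline mediators only where appropriate. The mediation models are then set out separately, in other terms and with another covariate rule. That rule contradicts the general one however change is read, so the point is more than missing detail.

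Three stronger readings are tempting, and the documents do not support them.

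- *Direct and mediated effects fail to add up to the reported effect.* The expected difference is zero, the difference in a single trial is chance, and the protocol promises no decomposition of the total.
- *Baseline behavior alone can produce a significant mediated effect.* The product also needs a non-zero α, which rests on the randomized comparison.
- *β is certainly badly biased.* That requires both the raw-change reading and a dependence that the documents do not quantify.

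**Conclusion.** The point holds in a limited form. The covariate rules for the α models contradict each other, and the β models are worded so that a literal reader would leave out the baseline outcome. On that reading β is biased in proportion to (r − 1) × λ. In the assumed range this means no error at λ = 0 and, at stability 0.5, between −48% and +34%, in either direction. On the residualized reading the attenuation is 0 to 18%. With the baseline outcome and baseline mediator in the model there is essentially no bias. These sizes rest on assumed values of r, λ and ρ, a linear model and a two-group contrast. Only the secondary mediation aim is touched; the primary comparisons are not. The change is worth making because it removes the risk at almost no cost.

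**What to change.** In the Data analysis section, specify the mediation models in the same form as the effect models:

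- **α model:** mediator at the assessment on the intervention terms, the baseline mediator and the prespecified covariates.
- **β model:** outcome at the assessment on the intervention terms, the mediator at that assessment, the baseline outcome, the baseline mediator and the same covariates.
- **Covariates:** one prespecified set for the effect, α and β models. Delete significance as the selection rule.

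Change scores may be kept if preferred. Once the baseline is in the model, subtracting it from the response only shifts the baseline's own coefficient by −1. Putting the baseline outcome in the α model as well makes direct plus mediated effect equal the total from the effect model with the same covariates; in the linear simulation the difference was below 1e-14.

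The cost is wording only. Outcomes and mediators are already collected at baseline. Change and residualized change already need those values, so the added baseline terms exclude no further children.
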